## Abstract

**Background:**

Benign paroxysmal positional vertigo (BPPV) is the most common type of vertigo. While BPPV is best treated with canalicular repositioning manoeuvres, they are not routinely performed in primary care (PC).

**Methods:**

To evaluate the effectiveness of blended training (online and face-to-face) on the diagnosis and management of vertigo to improve adherence of family doctors to clinical practice guidelines, we designed a community multicentre cluster-randomised open-label trial with an intervention (IG) and a control (GC) group of 10 primary care teams (PCT) each. Outcome variables will be ICD-10 diagnostic codes (proportion of nonspecific diagnoses such as dizziness and vertigo versus specific diagnoses such as BPPV, vestibular neuritis, and Menière’s disease); number of referrals to ENT or neurology specialists; prescription of antivertigo agents; and duration of sick leave due to vertigo. The baseline comparability of the two study groups will be analysed to ensure homogeneity. A description of all baseline variables will be performed. Student’s *t*-test will be used to evaluate the differences between the groups. Logistic regression multivariate analysis will be performed to study the relationship between baseline variables of professionals and centres with outcome variables.

**Discussion:**

With the improvement of the diagnosis and management of vertigo by family doctors after this training, we expect an increase in the proportion of specific diagnoses, a decrease in the prescription of antivertigo agents, a decrease in referrals to ENT or neurology specialists and a reduction in the duration of sick leave due to temporary disability. The blended training will be easily expanded within primary care services, since it is mainly delivered online, with a single face-to-face session to ensure that the manoeuvres have been adequately learned.

**Trial registration:**

ClinicalTrials.govNCT04929444. Registered June 18, 2021. This protocol has been approved by the Ethics Committee of the Institut Universitari d’Investigació en Atenció Primària Jordi Gol (IDIAP Jordi Gol) with the code 20/004-P. All patient data will be anonymised in agreement with the 2016/679 European Regulation.

**Supplementary Information:**

The online version contains supplementary material available at 10.1186/s13063-022-06548-7.

## Administrative information

Note: The numbers in curly brackets in this protocol refer to the SPIRIT checklist item numbers. The order of the items has been modified to group similar items (see http://www.equator-network.org/reporting-guidelines/spirit-2013-statement-defining-standard-protocol-items-for-clinical-trials/).

## Introduction

### Background and rationale {6a}

Dizziness affects 20–30% of people at some point in their lives [1]. Approximately 5% of primary care consultations are due to dizziness, and over 50% of patients with dizziness are firstly assessed by family doctors [2, 3].

Vertigo, defined as the sensation of spinning objects and instability, severely affects the quality of life, causes a twofold increase in the prevalence of functional disability, worsens symptoms of depression [4] and decreases participation in social activities and self-efficacy to prevent falls [5]. A total of 69.8% of patients with vertigo have to reduce their work activities, and 63.3% need to take sick leave for several days [6]. Vertigo is associated with high costs for health services [6].

Benign paroxysmal positional vertigo (BPPV) is the most common cause of peripheral vertigo, affecting between 17 and 42% of patients with vertigo [7]. Up to 85–95% of cases of BPPV affect the posterior canal (BPPV-PC), and the Dix-Hallpike test (DHT) is considered the gold standard for its diagnosis [7]. As shown in literature reviews [8–11], the Epley manoeuvres (EM) are the most effective for treating BPPV-PC [12]. Consequently, with the use of the DHT and the EM, patients can be quickly identified and treated during primary care consultations without the need for referral or expensive medical tests. Clinical practice guidelines recommend the DHT and the EM and advise against the use of medical tests (except in the few cases where the diagnosis is unclear) and against the use of antivertigo agents [7].

Despite these recommendations, 60 to 80% of patients are visited in PC and hospital emergency departments where these diagnostic and treatment tests are not routinely performed [13–15]. A study by Dunlap et al. (2019) [16] based on 20.6 million PC visits (95% CI 17.3, 24.0) for dizziness observed a low percentage of treatments such as repositioning manoeuvres and a frequent diagnosis of “nonspecific dizziness” (75%).

Three main reasons were given for not implementing these diagnostic and therapeutic procedures (especially DHT and EM) in primary care: (1) the evidence originates from studies conducted in clinics with specialists (2) with easy access to instruments that facilitate the visualisation of nystagmus during the DHT and (3) the lack of training on how to perform these manoeuvres [17].

To improve this situation, a German protocol of a cluster-randomised trial was published in 2018 to evaluate the benefits of a half-day training for GPs [18]. A similar study protocol for ER physicians published in the USA in the same year [19] showed that physicians in the intervention group were twice more likely to perform the DHT and EM than doctors in the control group [20].

Our group has recently published a clinical trial [21] in patients with BPPV-PC that compared the performance of a single EM with the simulated manoeuvres performed by family physicians who had participated in a 2-h training workshop. This trial demonstrated that after receiving brief training, GPs can effectively diagnose and treat patients with BPPV-PC. However, the real challenge is to integrate these diagnostic and treatment manoeuvres into the everyday practice of all primary care physicians.

The objective of this study is to assess if a training intervention for GPs can optimise the diagnosis and management of patients with vertigo.

### Objectives {7}

#### Hypothesis

Better training on the diagnosis and treatment of vertigo and BPPV will improve the adherence of professionals to the vertigo clinical practice guidelines.

#### General objective

The general objective is to evaluate the effectiveness of a blended training intervention (online and face-to-face) regarding adherence to the BPPV clinical practice guidelines for the diagnosis and management of vertigo in PC.

#### Specific objectives

The following are the specific objectives:Assess if the diagnostic codes of vertigo in the primary care teams (PCT) that have received the training (intervention group (IG)) have improved compared to PCT in the control group (CG): decrease of nonspecific diagnoses such as dizziness and vertigo and increase in specific diagnoses such as BPPV, vestibular neuritis, Menière’s disease (see Supplementary material 1 for the complete list of diagnoses considered specific and nonspecific)Assess if referrals to ear, nose and throat (ENT) and neurology specialists due to vertigo are lower in the IG compared to the CGAssess if there is a decrease in the prescription of antivertigo agents in the IG compared to the CGAssess if the sick leave duration (in days) in the IG is shorter than in the CG

### Trial design {8}

To measure the effectiveness of the training in the IG, we designed a community multicentre cluster-randomised open-label trial, with the PCT as the allocation unit. The professionals of the PCT in the IG will receive training at the beginning of the study. PCT in the CG will be offered the training after study completion. Adherence to clinical practice guidelines will be measured during the year after completion of training in each PCT.

## Methods: participants, interventions and outcomes (Fig. 1)

### Study setting {9}

The study setting is Metropolitana Sud Area – Catalan Institute of Health (ICS), which in 2016 had 56 PCT for a catchment population of 1,334,381 people, of which 1,042,920 had been visited during that same year. A random sample of 20 PCT will be chosen from the 56; 10 will be included in the IG, and 10 in the CG.

**Fig. 1 Fig1:**
[figure not shown]
Study flowchart

The study population is all patients seen by family physicians (GPs) working in the selected PCT in the Area Metropolitana Sud of the ICS.

The study periods are pre-intervention study period from January to December 2021 and post-intervention period from January to December 2022.

### Eligibility criteria {10}

The inclusion criteria are all patients assigned to the 20 randomised primary care teams of the 56 that make up the Southern Metropolitan Area of the Catalan Health Institute, which serves a population of 1.3 million people.

The following are the exclusion criteria:Primary care teams in which > 60% of their professionals have received a course on vertigo in the last 5 yearsPrimary care teams not interested in participating in the studPatients who die during the year before and after the training intervention.Patients who change PCT

### Who will take informed consent? {26a}

The study will use a pseudonymised database in the Information System for the Development of Research in Primary Care (SIDIAP).

The study researchers will organise a session to explain and discuss the clinical trial with the various PCT. An information leaflet with the main aspects of the trial and the consent forms will be provided. After this session, the researchers will obtain the consent of the physicians who wish to participate.

### Additional consent provisions for collection and use of participant data and biological specimens {26b}

This study will not collect biological samples.

No new studies or sub-studies based on these data are anticipated.

### Interventions

#### Explanation for the choice of comparators {6b}

##### Active comparator: training group

The professionals of the primary care teams in the intervention group will receive the training at the beginning of the study.

##### Other: training on vertigo

The 14-h web-based course on vertigo management in primary care will include theory and clinical cases. The course will contain videos purposely produced for this course. Feedback (correct or incorrect) will be provided after each answer. Participants can ask questions during the course on the online platform. After the online course, researchers will deliver a 90-min face-to-face session where all participants will perform the diagnostic and therapeutic manoeuvres and where these manoeuvres will be evaluated and standardised.

##### No intervention: regular primary care practice

The professionals of the primary care teams that are in the control group will be offered training after the completion of the study.

#### Intervention description {11a}

VERTAP clinical trial (training intervention to improve the management of vertigo in primary care).

The objective of this protocol is to evaluate the efficacy of blended online and face-to-face training on the diagnosis and treatment of vertigo, in order to improve the adherence of family doctors to clinical practice guidelines.

Using the CAMFiC Moodle platform, we will adapt a pre-existing course prepared by the VERTAP that will contain videos showing the main diagnostic and therapeutic manoeuvres for vertigo. The contents will be reviewed by family doctors, physiotherapists and an ENT specialist. It will conform to the objectives of the study, with interactive clinical cases to improve the diagnosis and treatment of patients with vertigo. The online course requires approximately 14 h of individual study. This course will have to be completed within 6 weeks from the moment of registration and access.

After training with ENT and vestibular rehabilitation specialists, medical researchers will conduct the face-to-face session to verify and discuss the correct performance of the manoeuvres. The face-to-face group session lasts approximately 90 min. It will be carried out by a pair of researchers going to the PCT, who will supervise each doctor’s implementation of the diagnostic and therapeutic manoeuvres learned in the online course. During this session, researchers will also standardise the diagnosis and management of vertigo. Once the study period is over, the CG will be offered the possibility of taking the course.

An online course follow-up team will send email reminders regarding the start, follow-up and completion of the course. VERTAP researchers will take the register in the face-to-face sessions.

The TIDieR checklist will be followed during the intervention.

#### Criteria for discontinuing or modifying allocated interventions {11b}

No specific criteria have been proposed for discontinuing or modifying allocated interventions, since for the patient they do not differ from routine consultations.

#### Strategies to improve adherence to interventions {11c}

The PCT in Catalonia are currently focused on the COVID-19 pandemic. We will start the intervention when regular primary care activity resumes.

To increase adherence to the online course, we will send weekly reminders to encourage participants to complete the course.

To ensure participation in the face-to-face sessions, we will implement the training in the PCT of participating physicians. The director of the PCT will decide the best date for the face-to-face training within a 4-month period.

#### Relevant concomitant care permitted or prohibited during the trial {11d}

The PCT that have received previous training on vertigo have been excluded.

Only participants in the intervention group will be able to activate the online platform during the 6 weeks. After completion of the study, participants in the control group will be offered the online and face-to-face training.

#### Provisions for post-trial care {30}

No damages or compensation are anticipated for study participants. Physicians in the IG not able to complete/to pass the course will be able to retake it together with the CG.

### Outcomes {12}

Data from the whole population assigned to participating PCT will be obtained from the Information System for the Development of Research in PC (SIDIAP) at baseline and during a year after the start of the training.

#### Exposure variable

Measurement will be based on primary and secondary outcomes.Primary outcome measures:Register of ICD-10 vertigo diagnoses: Specific diagnoses registered during the study: BPPV (H81.1), Menière’s vertigo (H81) and vestibular neuritis (H81.2). Unspecific diagnoses registered during the study: dizziness or vertigo (R42) and other peripheral vertigos (H81.3). The ratio of specific diagnoses: ratio of specific versus nonspecific diagnoses. Effectiveness: higher proportion of specific diagnoses and lower of nonspecific diagnoses in the IG compared to the CG (see Supplementary material 1 for the complete list of diagnoses considered specific and nonspecific)Secondary outcome measures:Percentage of patients treated with antivertigo agents (betahistine, sulpiride, dimenhydrinate) in relation to all patients with vertigo in the PCT. Effectiveness: less antivertigo agents prescribed in the IG compared to the CGPercentage of referrals to neurology and/or ENT due to vertigo (H81.1, H81.1, H81.3 and R42). Effectiveness: lower number of referrals in the IG compared to the CGTotal number of sick leave days due to vertigo in the IG. Effectiveness: less sick leave days in the IG compared to the CG

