#### Sample size {14}

To improve vertigo diagnostic codes, accepting an alpha risk of 0.05 and a beta risk < 0.2 in a two-sided test, a total of 356 patients are needed per group (IG and CG) to detect as statistically significant a difference of 30% and 40% in correct diagnoses (BPPV, vestibular neuritis, vestibular migraine and Menière’s disease) for the CG and IG, respectively, with no loss to follow-up anticipated (GRANMO calculator, Institut Municipal d’Investigació Mèdica, Barcelona, Spain, using the ARCSINUS approach). To evaluate the final sample size, we take into account that the intercluster correlation coefficient (ICC) most commonly used in cluster-randomised trials in PC is 0.05. This ICC translated to a size of 45 individuals (assuming 10 clusters per group) in the design is adjusted by 1.24, i.e. *n* = 712 × 1.24 = 884 (45 per centre).

Similarly, the comparison of expected variation proportions for the prescription of antivertigo agents is 58.21% and 48% for the CG and IG, respectively (374 per group before adjustment by design) and 20% and 10% for referrals to neurology and ENT (195 per group before adjustment for design). All proportion estimates are based on the results of the previously published study [20].

However, data from *all* patients with a new diagnosis of vertigo and dizziness during the study period (1 year after the intervention) in participating centres will be collected, ensuring a number greater than the sample calculation.

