### Data collection and management

#### Plans for assessment and collection of outcomes {18a}

The IG PCT will receive online and face-to-face training on the diagnosis and treatment of vertigo in general and of BPPV in particular, and also on the correct ICD-10 diagnostic codes. After the completion of the study, the CG PCT will be offered the same training. All data will be extracted from the SIDIAP pseudonymised database, a research platform that includes the computerised primary care medical records of 80% of the Catalan population.

Primary outcome: improvement in the specific and non-specific diagnoses of vertigo. Secondary outcome: comparison between the IG and CG of percentage of patients treated with antivertigo agents, and percentage of referrals to neurology and ENT.

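### The prescribing percentage uses a denominator that training can shift in either direction, and sick leave is an unscaled total that conflicts with the trial's own duration objective

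*Protocol article*

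**What the plan says.** Under Exposure variable, the protocol article measures prescribing as the share of patients given an antivertigo drug, "in relation to all patients with vertigo in the PCT". Success is a lower figure in the IG.

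Who counts as a vertigo patient is settled by routine records: "All data will be extracted from the SIDIAP pseudonymised database" (Plans for assessment and collection of outcomes {18a}). Sample size {14} says that the patients collected are all "patients with a new diagnosis of vertigo and dizziness during the study period (1 year after the intervention". The section on blinding says that nobody is blinded. IG teams are trained in diagnosis and treatment, "and also on the correct ICD-10 diagnostic codes"; control (CG) teams are offered the same training only after the study.

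Sick leave, also under Exposure variable, is a total count of days, worded for the IG alone and with no denominator. The criterion is "Effectiveness: less sick leave days in the IG compared to the CG". The Abstract and the Specific objectives describe this outcome as a duration. Section {18a} leaves sick leave out when it lists the secondary outcomes.

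Outcomes {12} adds: "Data from the whole population assigned to participating PCT will be obtained", at baseline and over the follow-up year.

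**The concern.** A percentage among coded patients conditions on something that happens after randomisation and that the intervention may influence. Analysing teams as randomised does not protect against this, because the patients are selected into the denominator later. If trained GPs give a listed code to more patients, or to fewer, the prescribing percentage changes even when the same people receive the same drugs. A reader would then take a coding effect for a change in care, or miss a real change.

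The sick-leave problem is separate. A total of days combines how many people a team serves, how many of them take leave, and how long each leave lasts. Only the last is the stated objective. Two analysts following different sections of the article would compute different quantities.

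**Working it through.** **1. The plan's own figure.** Inputs from Sample size {14}: "accepting an alpha risk of 0.05 and a beta risk < 0.2 in a two-sided test", and prescribing of "58.21% and 48% for the CG and IG, respectively (374 per group before adjustment by design". The arcsine method that the section names gives

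n = 2(z₀.₉₇₅ + z₀.₈₀)² / h², with h = 2·asin√0.5821 − 2·asin√0.48 = 0.205,

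so n = 2(1.960 + 0.842)² / 0.205² = 373.7 (h unrounded), which rounds up to the stated 374. The rates 58.21% and 48% are therefore the right reference points.

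**2. Changing the denominator with prescribing unchanged.** Let g be the relative growth in coded IG patients. Let q be the percentage of the added patients who receive a drug, and would have received it anyway. Then

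p = (58.21 + g·q) / (1 + g).

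With q = 0:

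| g | IG percentage |
|---|---|
| 5% | 58.21/1.05 = 55.4% |
| 10% | 58.21/1.10 = 52.9% |
| 15% | 58.21/1.15 = 50.6% |
| 20% | 58.21/1.20 = 48.5% |

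At g = 10% the shift is 58.21 − 52.92 = 5.29 points, about half of the planned 10.21.

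Setting p = 48 gives g = (58.21 − 48)/(48 − q):

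| q | g needed to show 48% |
|---|---|
| 0% | 10.21/48 = 21.3% |
| 10% | 10.21/38 = 26.9% |
| 20% | 10.21/28 = 36.5% |
| 30% | 10.21/18 = 56.7% |

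The opposite direction is equally possible. If 10% fewer patients are coded and all of those lost were undrugged, the figure rises to 58.21/0.90 = 64.7%. If a patient moves from R42 to H81.1, both listed, the denominator and the percentage stay the same. Both g and q are assumptions.

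**3. Assigned population as denominator.** The rate is the number of patients prescribed divided by the number assigned. If drug recipients are counted whether or not they carry a vertigo code, g does not enter.

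**4. Sick leave.** Total days = people assigned × episodes per person × days per episode. At equal days per person, the ratio of totals equals the ratio of sizes, so an IG serving 10% fewer people shows 10% fewer days.

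Sequence generation {16a} describes no stratification by size. The article gives no coefficient of variation (CV) for PCT size, so I assume 0.2 to 0.5. With 10 teams per arm, the standard error of the log ratio of totals is about CV·√(2/10), and the chance that the IG total is at least 10% lower through size alone is Φ(ln 0.9 / SE):

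| CV | SE | Chance |
|---|---|---|
| 0.2 | 0.089 | 12% |
| 0.3 | 0.134 | 22% |
| 0.5 | 0.224 | 32% |

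This is not a false-positive rate. When PCT totals that vary only through size are compared by t-test, simulation gives p < 0.05 in about 4.5% to 4.9% of trials, with 2.2% to 2.4% favouring the IG.

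**The case against.** The strongest reply is that the aim is guideline adherence in managing vertigo, for which a percentage among vertigo patients is the natural measure, and that the sample size is built on it. The expected effect is also replacement of nonspecific by specific codes. Both kinds are on the list, so replacement leaves the denominator alone. The training is described as covering diagnosis, treatment, manoeuvres and coding, not case-finding. All of this stands, and it is why the percentage should be kept rather than dropped.

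A reader might go further and infer that training does enlarge the IG denominator with milder cases and so manufactures a benefit. The documents do not support that: they give no growth figure, say nothing about the severity of added cases, and allow movement either way. The 21% figure is the extreme case in which no added patient receives a drug. Similarly, the primary shift from 30% to 40% could arise from adding 16.7 specific codes per 100 patients, since (30 + 16.7)/(100 + 16.7) = 40%. That assumes no nonspecific code is replaced, contrary to the first specific objective. Nor can the argument be carried over to referrals, whose denominator is not stated.

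It is also tempting to say that the trial could not distinguish coding from care. That is too strong. Population data are obtained before and after, and code counts are themselves outcome measures, so a rise in coded patients would be visible in the data. The weakness lies in the defined outcomes, not in the extraction.

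Supplementary material 1 and any analysis plan are not shown and may refine the definitions. They would not remove the conflict between a total and a duration within the article.

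**Conclusion.** The point holds in two parts, both on secondary outcomes.

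First, the prescribing percentage can move without any change in prescribing if training alters who receives a listed code. The direction is not known. The size depends on assumed growth: 10% growth with no drug among the added patients accounts for about half of the planned difference, and the whole of it needs 21% to 57% growth as prescribing among the added patients goes from none to 30%.

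Second, sick leave is defined as an unscaled total in one place and as a duration in others, and these must be reconciled. This needs no assumption. A reader might infer that unequal PCT size would produce spurious findings of benefit. It would not if PCT totals are the unit of comparison: size imbalance is then chance variation that costs power, and the error rate stays near 5%.

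**What to change.** - **Sick leave:** define it for both arms as vertigo sick-leave days per 1,000 assigned working-age patients per year in each PCT. Report mean days per episode beside it, to match the Specific objectives, and list the outcome consistently in {18a}.
- **Prescribing:** keep the percentage among coded patients. Add patients prescribed an antivertigo agent per 1,000 assigned patients per year, counted from prescription records regardless of code and adjusted for the PCT's 2021 rate.
- **Codes:** report specific and nonspecific codes per 1,000 assigned patients per year, with the same adjustment, beside the primary proportion. Added coding can then be told from replaced coding.

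The cost is outcome wording and a denominator that is already being extracted, assuming age is available to define working-age patients. Population rates are somewhat noisier, because they also reflect variation in consulting and any prescribing for other reasons. Sick leave attributed to vertigo still depends on the recorded code, and mean days per episode still conditions on episodes coded after randomisation. The 2021 rate is not a wholly clean baseline either, since the Participant timeline gives IG teams access to the online course in November and December 2021.

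### The referral outcome mixes percentage and number, names no denominator, and uses a code list that omits Menière's disease and (as printed) vestibular neuritis, which can modestly favour the intervention group

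*Protocol article*

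**What the plan says.** All references are to the Protocol article.

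- **Outcomes {12}, Exposure variable, secondary outcomes.** Referrals to neurology or ENT due to vertigo are defined as a percentage, with no statement of what it is a percentage of. The effectiveness line that follows reads "lower number of referrals in the IG". The codes in brackets are H81.1, H81.1 again, H81.3 and R42.
- **Same section, primary outcome.** Specific diagnoses are "BPPV (H81.1), Menière’s vertigo (H81) and vestibular neuritis (H81.2"). Nonspecific diagnoses are "dizziness or vertigo (R42) and other peripheral vertigos (H81.3"). The complete list is said to be in Supplementary material 1.
- **Same section, antivertigo outcome.** Here a denominator is given: "in relation to all patients with vertigo in the PCT".
- **Abstract, Methods.** The outcome is the "number of referrals to ENT or neurology specialists".
- **Plans for assessment and collection of outcomes {18a}.** The outcome is the "percentage of referrals to neurology and ENT". This section also says that the intervention teams are taught correct ICD-10 coding.
- **Sample size {14}.** The planning values are "20% and 10% for referrals to neurology and ENT", giving 195 per group before the design adjustment.

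**The concern.** There are two faults.

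First, the outcome is not one quantity throughout. A number of referrals and a percentage of patients referred are different measures. Without a denominator, even the percentage has two readings: the share of vertigo patients who are referred, or the share of referrals that are for vertigo. The planning figure fits only the first. The analysis is open-label ({17a}), so anything left open would be settled by people who know the allocation.

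Second, the referral code list does not match the list that defines vertigo for the primary outcome. Two codes are missing as printed, and both belong to diagnoses that the specific objectives expect to rise in the intervention group. The training itself moves patients between codes, so randomisation does not balance the loss. Referrals under the omitted codes would go uncounted more often in the trained arm, and the estimated benefit would be too large.

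**Working it through.** **1. Which quantity was planned?** Inputs from Sample size {14}: 20% v 10%, two-sided α = 0.05, power 80%, arcsine method.

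n per group = 2(z₀.₉₇₅ + z₀.₈₀)² / h², with h = 2·asin√0.20 − 2·asin√0.10.

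h = 0.9273 − 0.6435 = 0.2838, so n = 2 × 7.849 / 0.0805 = 194.9, rounded up to 195. The stated figure is reproduced. The same formula returns the plan's 356 (30% v 40%) and 374 (58.21% v 48%). The referral outcome was therefore planned as a comparison of two proportions of patients, not of counts.

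**2. Which codes are missing?**

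| Code in the primary outcome | Class | In the referral list? |
|---|---|---|
| H81.1 (BPPV) | specific | yes, twice |
| H81 (Menière's, as printed) | specific | no |
| H81.2 (vestibular neuritis) | specific | no |
| H81.3 | nonspecific | yes |
| R42 | nonspecific | yes |

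If the second H81.1 is a misprint for H81.2, Menière's is still missing.

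**3. Size of the recoding effect, with all vertigo patients as denominator.** Inputs:
- specific diagnoses 30% (control) and 40% (intervention), so a shift of 0.10 (Sample size {14});
- referral rate 20%, the planned control value, assumed here to be the same in both arms and for every code, so there is no true effect on referral;
- s, the share of the shift that goes to omitted codes. The document does not give it, so the range 0 to 1 is shown.

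Spurious difference = 0.20 × 0.10 × s = 0.02s, that is 2 × s percentage points.

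If the same share s of specific diagnoses carries an omitted code in both arms, the counted rates are 0.20 × (1 − 0.30s) and 0.20 × (1 − 0.40s):

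| s | Control | Intervention | Spurious difference |
|---|---|---|---|
| 0.10 | 19.4% | 19.2% | 0.2 points |
| 0.25 | 18.5% | 18.0% | 0.5 points |
| 0.50 | 17.0% | 16.0% | 1.0 point |
| 1.00 | 14.0% | 12.0% | 2.0 points |

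**4. Could this alone be significant?** With the plan's 884 patients, 442 per arm, and ignoring clustering, power is about 4% for 18.5% v 18.0%, 6% for 17% v 16% and 14% for 14% v 12%. The last contrast would need about 4,438 per arm for 80% power. All new vertigo patients in the 20 centres will be collected, so the arms may well exceed 442, but clustering works the other way.

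**5. The same, with the short list as denominator too.** If a proportion u of patients carries omitted codes, the counted rate is 0.20(1 − u) / (1 − u) = 0.20 in both arms, whatever u is. At equal referral rates the artefact is zero. Its existence therefore depends on the denominator that the protocol does not name.

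**The case against.** A fair defence makes five points.

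- **The effectiveness lines give an expected direction, not a decision rule.** The antivertigo line is as loose, and Statistical methods {20a} sets tests at 5%. This stands. A reader might infer that effectiveness could be declared merely because the intervention teams are smaller and make fewer referrals in total. The document does not support that: no rule compares raw totals, size imbalance under randomisation is chance and can go either way, and in a team-level test on counts it would mainly add variance.
- **Most of the document treats the outcome as a percentage.** This also stands. Number appears only in the abstract and the effectiveness line, so the conflict is easy to resolve. It is still a conflict within one outcome definition, and the missing denominator remains.
- **The recoding bias assumes a particular denominator.** Correct, as step 5 shows. The all-vertigo denominator is nevertheless the one the neighbouring antivertigo outcome uses.
- **The effect is small.** The training stresses BPPV, which the article calls the most common cause of peripheral vertigo and which is counted, so s is probably well below 1. A reader might infer that recoding alone could make the training look effective; step 4 does not support this.
- **The duplicate code looks like a misprint, and the complete list is in a supplement.** A deliberate exclusion cannot be inferred. But the supplement is cited for the specific and nonspecific diagnoses of the primary outcome, whereas the referral outcome prints its own list, and no single-code correction restores both missing codes.

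**Conclusion.** The point holds as a defect in the definition of a secondary outcome. As written, the outcome is a percentage without a denominator, described elsewhere as a number, with a code list that does not match the trial's own definition of vertigo.

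With all vertigo patients as denominator, the list inflates the apparent benefit by 2 × s points, at most 2 of the planned 10. That ceiling rests on the plan's 10-point shift and on recoded patients being referred at 20%; a different referral rate among them would scale it in proportion. At equal referral rates the inflation is zero if numerator and denominator share the short list. It would distort the estimate without normally creating a significant result. It should be corrected, but it does not threaten the primary outcome.

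**What to change.** 1. Define the outcome as the percentage of all patients with vertigo in the PCT who are referred to ENT or neurology, with the same denominator as the antivertigo outcome.
2. Use the primary outcome's full specific and nonspecific code list, including H81 and H81.2, for both numerator and denominator, and remove the duplicated H81.1.
3. Replace number with percentage in the abstract and in the effectiveness line of Outcomes {12}. The Sample size and {18a} sections already speak of percentages.

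The change should be recorded before outcome data are examined by arm, because the analysis is open-label. The cost is a few words of protocol text and one change to the SIDIAP extraction query. No additional patients or data collection are needed.
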